## 6.7 Preparation and labelling of Investigational Medicinal Product

Production of cannabis flos (the whole dried flower) is strictly regulated by the Dutch government. The task for this regulation is seeded with the Office of Medicinal Cannabis (Bureau voor Medicinale Cannabis (BMC, part of Ministerie van VWS)). The raw material (cannabis flos) is produced by Bedrocan BV, Veendam NL (GMP with a constant composition of cannabinoids and terpenes).

Bedrocan produces standardized Active Pharmaceutical Ingredient (API). These products are used by the pharmaceutical industry, and meet the needs of large and small drug developers. This is because every stage of the manufacturing process is GMP-certified. Bedrocan is the world's only GMP producer of standardized, full-flower, medicinal cannabis. It offers both blended and genetically distinct herbal preparations suitable to develop novel, cannabis-based medicines. Bedrocan produces standardized cannabis flos for the Office for Medicinal Cannabis (OMC), the government office with a monopoly on medicinal cannabis supply to Dutch pharmacies, and on its import and export. The OMC is also responsible for overseeing the production of cannabis for medicinal and scientific purposes, guaranteeing quality through supervision of the grower and distributor.

The Transvaal Pharmacy in The Hague was the first pharmacy to produce cannabis oil after the OMC asked them to make formulation suitable for children. Cannabis oil is comprised of a concentrated soft extract obtained by extraction of the dried flowers of the cannabis plant and pharmaceutical grade vegetable oil. The purpose of producing cannabis oil is to make cannabinoids and other beneficial components, such as terpenes, available in a highly concentrated form and to provide an alternative route of administration (other than smoking, vaporization or orally).

In the Netherlands, pharmacies can't apply for a manufacturers authorization. For this reason, Felix Farma, which is a related party of Transvaal Pharmacy, has applied for this authorization. Currently, authorization is granted. A manufacturer authorisation number will soon be created by Farmatec.

Felix Farma will produce and label the cannabis oil. Transvaal Pharmacy will distribute the oil to the patients.

For more details see *D5\_Productgegevens apothekers* and *D3\_Voorbeeldetiketten*.

## **6.8 Drug accountability**

Full drug accountability will be performed by Felix Farma B.V. In accordance with good clinical practice (GCP) guidelines. For more details see *D5\_Productgegevens apothekers*.

## **7. NON-INVESTIGATIONAL PRODUCT**

Not applicable

## 8. METHODS

### 8.1 Study parameters/endpoints

#### 8.1.1 Main study parameter/endpoint

- A reduction of 30% and 50% of mean pain scores (of the pain quality “unpleasantness”) between Transvamic and placebo group.  
*Will be measured as the difference in mean scores pre- (baseline) and post-intervention (Transvamic and placebo) for each group using the pain quality items for “unpleasantness” from the short-form McGill Pain Questionnaire 2 (SF-MPQ2), a 22-item numerical rating scale (NRS 0-10) survey on pain qualities.*

#### 8.1.2 Secondary study parameters/endpoints.

- The difference of mean scores of pain qualities between Transvamic and placebo.  
*Will be measured as the difference of the mean of all SF-MPQ2 pain quality items (which have received a score >0 on NRS) between Transvamic and Placebo.*
- The difference of mean scores of pain intensity between Transvamic and placebo.  
*Will be measured as daily changes in pain intensity (1-14 days placebo, 1-14 days Transvamic) using the VAS-Pain ([no pain] 0-100 [worst pain imaginable] unit scale) for pain intensity. The change score (delta) from baseline to Transvamic (day 14) and Placebo (day 14) will be calculated.*
- To determine the effect of Transvamic on pain self-efficacy  
*Will be measured using the PSEQ survey pre-intervention (1x baseline) and during intervention (1x Transvamic, 1x placebo), a 10-item survey on the ability to continue normal life given ongoing pain.*
- The difference of mean scores of pruritus intensity between Transvamic and placebo.  
*Will be measured as daily changes in pruritus intensity (1-14 days placebo, 1-14 days Transvamic) using the VAS-Pruritus ([no pruritus] 0-100 [worst pruritus imaginable] unit scale) for pruritus intensity. The change score (delta) from baseline to Transvamic (day 14) and Placebo (day 14) will be calculated.*
- The difference in brain connectivity of the seed regions (anterior cingulate cortex and amygdala) to the brain cortex between Transvamic and placebo.  
*Will be measured using voxel-based analysis of blood oxygen-level dependent functional magnetic resonance imaging (fMRI-BOLD).*

- To determine sub-side effect threshold maintenance dose achieved of Transvamic during titration and the respective interindividual variability (CV%).  
*Will be measured as the dose administered on day 14 of placebo and Transvamic interventions. CV% is measured as inter-participant variance of dose achieved on day 14 of placebo and Transvamic interventions.*
- To inventorize how many and which participant-experienced adverse-events during titration and maintenance of Transvamic and the patient reported burden for each adverse event on numeric rating scale (NRS [not burdensome at all] 0-10 [extremely burdensome]).

## 8.2 Randomisation, blinding and treatment allocation

Blinding and the master file to blinded data will be managed by Felix Farma B.V. Randomization to each treatment arm will be completed by Felix Farma B.V. (see *D5\_Productgegevens Apothekers*).

## 8.3 Study procedures

After meeting all the inclusion criteria and enrolling participants in this study, all reported outcomes including both research clinician and participant reported survey will be recorded in the online case report forms (CRF) built into the traceable research program RedCap. The clinical research office at the UMCG will ensure the PI, research clinician and monitors have access to the CRFs and outcome measurement data in RedCap. Participants will receive URLs to access the surveys for online completion from a smartphone, tablet or computer.

### 8.3.1 Daily participant logbook completed by participants.

Participants will complete a logbook consisting of 3 parts each day in the evening (table 1) throughout the study period during which the participant received either Transvamic or placebo:

- Visual analog scales for pain and pruritus (VAS [no pain] 0-100 [worst pain/pruritus imaginable] units). These will be completed in the evening. Participants will be asked to complete VAS pain/pruritus retrospectively about the same day, subdivided into 3 timepoints in the day (*morning, afternoon and evening [or now]*).  
The periods of completion are as follows: Firstly, for baseline measurements (day -8 to -1) followed by Transvamic and placebo interventions (days 1 - 14 and 29 – 42).

- The titration scheme will be visualised and a checkbox ticked by the participant indicating the day of titration that was completed.
- Side effects will be reported following a multiple choice list\*, and the burden of the noted side effect indicated using numeric rating scales (NRS [not burdensome] 0-10 [extremely burdensome])
- Use of breakthrough medication or changes in analgesic medication recorded by participant.

\* Multiple choice list of side effects are categorized (in Dutch):

1. High gevoel (een vrolijke opgewekte stemming die langzaam overgaat in een tevreden gevoel van kalmte en rust).
2. Loomheid
3. Honger
4. Intensere beleving van kleuren en/of geluiden
5. Verlies van gevoel voor tijd en/of plaats
6. Sombere en/of angstige stemming
7. Rusteloosheid en/of slapeloosheid
8. Waanvoorstellingen
9. Versnelde hartslag
10. Duizeligheid
11. Warm of koud gevoel in handen en voeten
12. Rode branderige ogen
13. Spierverslapping
14. Droge mond
15. Anders, namelijk.....

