### 3. STUDY DESIGN

The study design is an *explorative randomized, placebo-controlled and double-blind intervention crossover study: Transvamix (100mg/mL THC / 50mg/mL CBD) to treat chronic pain in Epidermolysis Bullosa*. For further overview, see Table 1. Sixteen (16) participants will be enrolled for this study.

This is an explorative study because cannabinoid-based medicines (CBMs), Transvamix-like drugs, have not yet been studied by way of controlled trials in the EB patient population.

The addition of placebo mitigates confounding participation bias. The crossover design reduces the number of participants required, an important factor when studying rare diseases, and supported by randomization and blinding, enables rigorous statistical analyses. In addition to this, both intra-participant outcomes as well as group analyses by intervention type can be analysed.

Participants will receive both the IMP (Transvamix) and placebo in forward or reverse orders, depending on treatment arm allocation. The study drugs (Transvamix & placebo) will be provided by Felix Farma, and dispensed by the Transvaal pharmacy. A washout of two weeks between both interventions will mitigate carry-over effects as up to 80-90% of THC is excreted via the urine within 5 days (terminal elimination half life of 21.5 hours), and the elimination half-life of CBD is between 1.44 and 10.86 hours after oromucosal spray administration (5–20 mg). The duration of participation is 9 weeks. All participant reported outcome measurements (PROMs) are completed online, at home.

| Table 1: Table of Study-related Activities for the duration of C4EB |                             |                                    | Until day -8          | Day -7 to -1                                       | Day 1 to 14                                        | Day 15 to 28            | Day 29 to 42                                                   | Day 55                                                                           |
|---------------------------------------------------------------------|-----------------------------|------------------------------------|-----------------------|----------------------------------------------------|----------------------------------------------------|-------------------------|----------------------------------------------------------------|----------------------------------------------------------------------------------|

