|                                                                     | Time required               | Location                           | Eligibility Screening | Before intervention with Transvamic-oil or Placebo | Titration and Maintenance of Transvamic or Placebo | Washout Period (no IMP) | (Crossover) Titration and Maintenance of Transvamic or Placebo | Structured interview on study participation, events and feedback on methodology. |
| Eligibility Screening; NRS pain; medication recording               | 60 minutes                  | Video conference / telephone       | Completed             |                                                    |                                                    |                         |                                                                |                                                                                  |
| Transvamic or Placebo administration                                | N/A                         | Administered at home               |                       |                                                    | Administration following titration scheme          |                         | Administration following titration scheme                      |                                                                                  |
| PROM:
*(DN-4; CSI; HADS; PCS; SF-MPQ2; PSEQ)
**( MPQ2; PSEQ)  | *40 minutes
**20 minutes | Online survey completion at home   |                       | (day -1)*                                          | (day 14)**                                         |                         | (day 42)**                                                     |                                                                                  |
| Logbook (VAS Pa/Pr , dose administered, side-effects)               | 10 minutes                  | Online survey completion at home   |                       | (daily)                                            | (daily)                                            |                         | (daily)                                                        |                                                                                  |

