#### **8.3.5 Follow-up Structured Interview**

Participants who have completed participation, or who have dropped out (and have given consent for regular follow-up) will be contacted by telephone or video conferencing by the research clinician. The interview will consist of 3 parts:

1. General perspectives on participation (related to recruitment and study design)
2. General perspectives on interventions (related to Transvamic and placebo).
3. General and specific feedback for future studies pertaining to CBMs as interventions and/or EB patients.

Directly following the structured interview, participants will be sent via email an automated researcher-blinded question on the order of interventions received (the responses will be unblinded after statistical analysis of the study is completed). The options are: I) Transvamic → Placebo, II) Placebo → Transvamic, III) I don't know.

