### 9.2 AEs, SAEs and SUSARs

#### 9.2.1 Adverse events (AEs)

Adverse events are defined as any undesirable experience occurring to a subject during the study, whether or not considered related to Transvamic or placebo. All adverse events reported spontaneously by the subject or observed by the investigator or his staff will be recorded.

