doses required for experienced side effects from either CBD or THC in TransvamiX-oil. The possible acute onset side effects, such as dizziness or an increased appetite are short lasting (1-2 hours, and completely withdrawn 4-8 hours after administration) and can be avoided by reducing the following dose administered to the previous step in the titration scheme. In case of accidental overdose, patients are advised to go to a quiet area and just wait until the adverse effects wear off. In case of emergencies patients will have access to adequate medical support.

k. Why are both THC and CBD present in the study medication?

Clinical studies have shown that the combination of THC and CBD are superior to either cannabinoid alone. Additional CBD has been shown to reduce the unwanted side effects of THC administration through receptor antagonism, making the combination more preferable to patients receiving CBM treatments .

l. Are cannabinoid-based medicines addictive?

The key component responsible for the psychotropic effects and dependence potential of cannabinoid-based drugs is THC, acting on pathways in the central nervous system. Substance abuse can have both physical and psychological influences. Dependence is preceded by an increased tolerance to the drug and negative withdrawal symptoms, followed by psychosocial consequences.

To address the former, a review of a CBM (comprising THC and CBD) in 2011 with >1500 patient-years of treatment experience showed the absence of increased tolerance to the study drugs – i.e. the dose remained the same throughout the studies or even was reduced . Dutch data on the number of CBM prescriptions show an unchanged duration of use (first dispensation to last dispensation) between 2003-2011 and 2012-2016, and the average daily administration remaining remarkably stable .

The abuse potential of CBMs comprising THC however cannot be directly compared with commercial THC preparations as the underlying motivation to administer the drug in disease is to relieve symptoms in the absence of side-effects. In addition to this the administration form used most often recreationally, with a higher risk for abuse, is intrapulmonary, with higher percentages of active THC, leading to fast onset and high plasma peaks, and an increased chance for withdrawal symptoms . This is not the case in current regulated CBMs following dose-titration schemes with supervision.

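### The prompted side-effect logbook has no entry after the last late-evening dose of each period (days 14 and 42), and section 8.3.5 lists no explicit adverse-event question

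*Protocol*

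**What the plan says.** Section 8.3.1 asks participants to complete the logbook every evening "throughout the study period during which the participant received either Transvamic or placebo". It dates the visual analogue scales to baseline, "followed by Transvamic and placebo interventions (days 1 - 14 and 29 – 42". Those days stand under the pain and pruritus item, but Table 1 gives the same periods for the whole logbook. Its row reads "Logbook (VAS Pa/Pr , dose administered, side-effects" and is marked daily at baseline and in the two dosing periods, with no mark in the washout column or after day 42.

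Table 2 schedules the last dose of each day at 9PM-12AM. Section 1.2 puts maximum THC concentration at 2-3 hours after oromucosal absorption. Section 13.1 j describes acute side effects as short and "completely withdrawn 4-8 hours after administration".

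Outside the logbook, section 9.2.1 states: "All adverse events reported spontaneously by the subject or observed by the investigator or his staff will be recorded". Table 1 describes the day 55 contact as "Structured interview on study participation, events and feedback on methodology". Section 8.3.5 lists three parts for that interview: perspectives on participation, perspectives on the interventions, and "General and specific feedback for future studies pertaining to CBMs as interventions and/or EB patients". None is expressly an adverse-event enquiry.

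Frequency and burden of adverse events during titration and maintenance is a secondary endpoint (8.1.2). The dose achieved is read on days 14 and 42 (10.2.2).

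**The concern.** The logbook works by catching a late-evening reaction at the next evening's entry. On days 1 and 2 the only dose is the late-evening one, so the design already depends on this. It works for scheme days 1 to 13 and fails on the last day of each period, which has no following entry.

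Two stated outcomes are touched. A reaction to the last maintenance dose belongs to the adverse-event endpoint even when it is felt after midnight, but it is neither prompted nor given a 0-10 burden score. Side effects also define the threshold maintenance dose (6.6). A participant who completes the scheme and reacts overnight to the final dose could therefore be counted as tolerating 75 mg THC with no logged side effect. The later contact that might recover the event is described differently in Table 1 and in 8.3.5.

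**Working it through.** **Inputs.** Dose volumes and clock windows: Table 2. Strength: 100 mg/mL THC and 50 mg/mL CBD. Time to peak 2-3 h: section 1.2. Acute effects gone by 4-8 h: section 13.1 j. Logbook days: 8.3.1 and Table 1.

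**Reproducing the plan's top dose.** Day 14: 0.2 + 0.15 + 0.2 + 0.2 = 0.75 ml. 0.75 × 100 = 75 mg THC and 0.75 × 50 = 37.5 mg CBD, as stated. All 14 row totals in Table 2 agree with their components.

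**Timing of the last dose.**

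| | Dose at 9PM | Dose at 12AM |
|---|---|---|
| Peak (+2 to 3 h) | 11PM-12AM | 2AM-3AM |
| Cleared (+4 to 8 h) | 1AM-5AM | 4AM-8AM |

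An entry made before or shortly after the last dose precedes the peak. Even someone who doses at 9PM and logs just before midnight misses the tail.

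**How much of the exposure is affected (full titrator).**
- Scheduled doses per period: 1 + 1 + 2 + 3 + (10 × 4) = 47. One has no later entry: 1/47 = 2.1%.
- Total volume per period is 4.75 ml: 0.2/4.75 = 4.2%.
- Share of day 14: 0.2/0.75 = 26.7%. The other 0.55 ml (73.3%) is scheduled by 7PM.
- Four administrations in the scheme are 0.2 ml: day 13 late evening, and day 14 morning, 4PM-7PM and late evening. Three of them precede the day 14 entry.

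**Participants who stop titrating earlier.** The dose that triggered the side effect is followed by further logged days at the reduced dose. For them the unlogged final dose repeats a level already observed. The effect on the threshold dose therefore concerns full titrators. Under 6.6 a logged reaction moves the participant back one scheme day, and the day 13 total is 65 mg THC against 75 mg on day 14.

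**What remains as back-up.** Day 55 is 55 − 14 = 41 days after the end of period 1 and 55 − 42 = 13 days after the end of period 2, so recall at interview would be unequal between periods.

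**With the fix.** One entry on days 15 and 43 puts 47 of 47 doses per period before a logbook entry.

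**The case against.** The other side has several good points.

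- **Adverse events are not confined to the logbook.** Section 9.2.1 covers the whole study, 9.4 follows known events until they resolve or stabilise, and the DSMB monitors events throughout. This stands: what is lost is the prompt and the burden score, not the possibility of recording.
- **No clock time is given for the evening entry.** Participants tick the scheme day they completed, which fits an entry after the last dose. This is fair, but such an entry would still miss part of the 4-8 h window.
- **The interview headings are not a script.** The part on the interventions could hold side effects. This is also fair, so the mismatch with Table 1 is one of wording. One explicit question removes the doubt.

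A reader might infer more than the document supports:

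- **That top-dose events are systematically missed.** They are not: 73.3% of the day 14 volume and three of the four 0.2 ml doses precede the last entry.
- **That section 13.1 l names withdrawal as a risk of this product.** It ties the raised chance of withdrawal symptoms to inhaled recreational use and says that this does not apply to regulated products titrated under supervision.
- **That the comparison with placebo is shown to be biased toward no difference.** Late drug effects could arise only after the active product, so an under-count would fall mainly there. But the protocol gives no rate for such events and plans only descriptive summaries, so no bias is shown.
- **That the log must run for the whole elimination time.** With the "terminal elimination half life of 21.5 hours" (section 3), 0.5^(24/21.5) = 46% of THC remains at 24 h and 0.5^(120/21.5) = 2% at 5 days. These are not event rates, and events after stopping lie outside the 8.1.2 endpoint.

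**Conclusion.** The point holds in a limited form, as a cheap improvement. The last dose of each period is the only one with no following prompted, burden-scored entry. For a full titrator this is 1 of 47 scheduled doses per period, or 0.2 of the 0.75 ml on the single 75 mg THC day. A reaction to it rests on spontaneous report or on an interview whose listed content does not expressly ask.

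This assumes that the final dose is taken in its Table 2 window, that the evening entry is made before or shortly after it, and that the protocol's 2-3 h and 4-8 h figures apply. It also assumes that reactions to earlier late-evening doses are picked up at the next evening's entry. The document gives no basis for the number of participants affected. How dosing should end is a clinical matter and is not judged here.

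**What to change.** 1. In 8.3.1 and Table 1, schedule one further side-effect and burden entry on days 15 and 43, asking about the time since the previous entry. Attribute it to the preceding intervention and state in 8.1.2 that it counts toward the adverse-event endpoint.
2. Add an explicit adverse-event question to 8.3.5, so that the day 55 interview matches its description in Table 1.

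Cost: a protocol and e-diary scheduling change, two short entries per participant (32 across 16 completers) and one interview question. No extra visits or staff are needed and dosing is unchanged.

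Optional: keep the side-effect part open through days 15-20 and 43-48 (6 + 6 = 12 entries per participant) if the sponsor also wants a prompted description of the days after stopping. The point above does not require it.

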Pain however is a multidimensional experience comprising physical (nociceptive) and emotional/psychological (conditioning) components. An additional challenge in EB patients is that most patients suffer from pain caused by multiple physical and pathophysiological aetiologies. A well-known example of this, which has been described in all EB subtypes, is chronic neuropathic pain accompanied by continuous nociceptive pain from chronic wounds and inflammation of the skin or mucosa. Adding further burden is the psychological response (pain affect) to chronic pain that exacerbates and worsens one's experiences of pain. The role of nociplastic pain (pain that arises from altered nociceptive function) has not been investigated in EB, however given its postulated role in chronic pain conditions, may indeed be relevant in EB-related pain. Due to this complex nature of chronic pain in EB, adequate analgesia is not achieved by single pharmacologic interventions, and on the contrary, the side-effect burden of poly-analgesic-pharmacy outweighs the decision to prescribe multiple pharmacologic interventions.

In a recent cross-sectional study on EB in the Netherlands, patients rated 20 qualities of pain. The highest score in all subtypes in the cohort was that for an “unpleasant” quality of pain. This is interesting as research has shown that pain affect, located in the limbic system, which is reported by patients as the pain quality “unpleasantness”, is functionally distinct from sensory pain processing pathways. One way to measure pain affect is using functional magnetic resonance imaging (fMRI) techniques to measure brain connectivity in known and suspected areas processing pain affect. Numerous studies using this technique have identified the amygdala and anterior cingulate cortex (ACC) as central brain areas that alter connectivity during chronic pain. Furthermore, independent of the aetiology of chronic pain, all chronic pain states (measured by fMRI) show similarities in altered brain connectivity, which are subsequently reversed (improved) with successful treatments.

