## 6.6 Dosages, dosage modifications and method of administration

Transvamic and placebo are administered sublingually using a 1 millilitre dosing syringe. All participants will follow the predetermined titration scheme (*Table 2*). The titration will be stopped at the onset of side-effects (as reported by the participant), and the dose administered reduced by one day in the titration scheme. This will be called the sub-side effect threshold maintenance dose.

This achieved dose will be maintained for the remaining intervention period until day 14 is completed for each intervention (Transvamic and placebo). Both placebo and IMP (Transvamic) will undergo the same titration scheme.

The maximum dose is 0.75ml/day Transvamic or placebo (divided between 4 separate administrations).

For additional information please see *D1\_Investigators Brochure* chapter 5.3.1.

| Table 2: Titration Scheme                                 |           |          |           |            | Total   | Total THC | Total CBD |
|------------------------------------------------------------------|-----------|----------|-----------|------------|---------|-----------|-----------|
| Transvamic (100mg/mL THC & 50mg/mL CBD) & Placebo |           |          |           |            | (ml)    | (mg)      | (mg)      |
| Day                                                              | 6AM – 9AM | 11AM-2PM | 4PM – 7PM | 9PM – 12AM |         |           |           |
| 1                                                                | -         | -        | -         | 0,05 ml    | 0,05 ml | 5         | 2,5       |
| 2                                                                | -         | -        | -         | 0,05 ml    | 0,05 ml | 5         | 2,5       |
| 3                                                                | 0,05 ml   | -        | -         | 0,05 ml    | 0,1 ml  | 10        | 5         |
| 4                                                                | 0,05 ml   | -        | 0,05 ml   | 0,05 ml    | 0,15 ml | 15        | 7,5       |

|    |         |         |         |         |         |    |      |
|----|---------|---------|---------|---------|---------|----|------|
| 5  | 0,05 ml | 0,05 ml | 0,05 ml | 0,05 ml | 0,2 ml  | 20 | 10   |
| 6  | 0,05 ml | 0,05 ml | 0,05 ml | 0,1 ml  | 0,25 ml | 25 | 12,5 |
| 7  | 0,1 ml  | 0,05 ml | 0,05 ml | 0,1 ml  | 0,3 ml  | 30 | 15   |
| 8  | 0,1 ml  | 0,05 ml | 0,1 ml  | 0,1 ml  | 0,35 ml | 35 | 17,5 |

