### 10.2 Secondary study parameter(s)

#### 10.2.1 Participant Reported Outcome Measurements (PROMs)

For all PROMs (SF-MPQ2 [all items], PSEQ [all items] and VAS pain/pruritus), descriptive statistics will be employed to portray means and standard deviations or medians and interquartile ranges for the measurements: baseline, placebo and Transvamic. The number of adverse events, and the participant reported burden of each, will be presented for each group (placebo and Transvamic) using frequencies of reported adverse events, means with standard deviations or median with interquartile ranges (depending observed distribution).

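### Side-effect logging before treatment is contradictory between section 8.3.1 and Table 1, and the adverse-event summary has no baseline, so symptoms present before dosing can be counted in both periods

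*Protocol*

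**What the plan says.** **When the logbook is kept.** The opening sentence of section 8.3.1 covers every part of the logbook and places it "throughout the study period during which the participant received either Transvamic or placebo". A baseline period appears only inside the bullet on the visual analogue scales: "Firstly, for baseline measurements (day -8 to -1) followed by Transvamic and placebo interventions (days 1 - 14 and 29 – 42". The side-effect bullet ("Side effects will be reported following a multiple choice list", each with a 0-10 burden rating) has no dates of its own.

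**Table 1 (section 3).** A single row, "Logbook (VAS Pa/Pr , dose administered, side-effects", is marked daily in three columns: days -7 to -1, days 1 to 14 and days 29 to 42. The first of these is headed "Before intervention with Transvamic-oil or Placebo". The washout column is blank.

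**How adverse events are summarised.** Section 10.2.1 says: "The number of adverse events, and the participant reported burden of each, will be presented for each group (placebo and Transvamic". The same section describes the questionnaires and scales at three measurements: baseline, placebo and Transvamix.

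**What counts.** Section 9.2.1 includes any undesirable experience during the study, related to treatment or not. Section 8.1.2 takes an inventory of events during titration and maintenance. Neither requires an event to be new or worse than before dosing. The frequency and burden of adverse events is a secondary objective in section 2.3.

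**The concern.** Many items on the section 8.3.1 checklist are non-specific: lethargy, low or anxious mood, restlessness or insomnia, dizziness, dry mouth, red burning eyes, warm or cold hands and feet. Participants have chronic symptoms and stay on their existing analgesic and antipruritic drugs (section 5.2). The protocol also measures anxiety and depression before treatment (section 8.3.2). It is plausible that some participants have a listed symptom before the first dose.

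Without a pre-dose record, such symptoms cannot be told apart from those that start on treatment. The frequency reported for each period would then mix background with treatment effect, and the difference in the proportion of participants affected can shrink. With 16 participants, a few people who report the same complaint in both periods matter for how that summary reads. Baseline symptoms that were never collected cannot be recovered by any later analysis plan.

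**Working it through.** The protocol gives no figure on this point, so there is none to reproduce. The check compares the passages and then illustrates direction and possible size.

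**1. Collection schedule**

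| Item | Section 8.3.1 | Table 1 |
|---|---|---|
| Pain and pruritus scales before treatment | Yes, from day -8 (8 days) | Yes, from day -7 (7 days) |
| Side effects before treatment | No dates; falls under the on-treatment opening sentence | Marked daily, days -7 to -1 |
| Dose before treatment | No dates | Marked daily, though no dose is given |

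Table 1 also assigns the time up to day -8 to eligibility screening, so the start day differs as well as the content.

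**2. Analysis under each reading**

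- If Table 1 governs, baseline side effects are collected, but section 10.2.1 gives them no use.
- If section 8.3.1 governs, they are not collected.

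Either way the adverse-event summary has two columns and no baseline, while the other participant-reported outcomes have three.

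**3. Participant-level illustration (all rates assumed)**

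Let b be the chance that a participant has a listed symptom regardless of treatment. Let q be the chance of a new symptom in a period, independent of b. If background symptoms are ticked, the recorded proportion is 1 - (1 - b)(1 - q), and the recorded difference between periods is (1 - b)(qT - qP). Take qT = 0.60 for Transvamix and qP = 0.20 for placebo:

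| b | Transvamix | Placebo | Difference | Ratio |
|---|---|---|---|---|
| 0 | 0.60 | 0.20 | 0.40 | 3.0 |
| 0.10 | 1 - 0.9 × 0.4 = 0.64 | 1 - 0.9 × 0.8 = 0.28 | 0.36 | 2.3 |
| 0.30 | 1 - 0.7 × 0.4 = 0.72 | 1 - 0.7 × 0.8 = 0.44 | 0.28 | 1.6 |
| 0.50 | 1 - 0.5 × 0.4 = 0.80 | 1 - 0.5 × 0.8 = 0.60 | 0.20 | 1.3 |

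A second set of assumed inputs (qT = 0.40, qP = 0) gives the same differences, because qT - qP is again 0.40: 0.36, 0.28 and 0.20. Of 16 participants, the expected reporters on Transvamix rise from 6.4 at b = 0 to 7.4, 9.3 and 11.2; on placebo they rise from 0 to 1.6, 4.8 and 8.0.

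**4. Event counts behave differently**

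If background adds m events to each period and the drug adds d, the counts are m + d and m. The difference is still d. Absolute counts are inflated, but the difference is not diluted unless a drug-caused symptom falls on an item already ticked. Section 10.2.1 speaks of numbers and frequencies of events, so the dilution in step 3 applies to participant-level summaries only.

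**The case against.** **The contradiction may be only loose wording.** The Table 1 row also covers dose, which cannot apply before treatment, so its baseline entry may be meant for the scales alone. This is a fair reading, and a reason to clarify. It does not settle what is collected, and it leaves the analysis gap in place.

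**Participants may filter out usual complaints.** The logbook asks for side effects, a term that invites attribution to the treatment. This stands: a reader might infer that long-standing symptoms will be ticked from day 1 in both periods, but the protocol shows only that they can be. No instruction in the protocol secures consistent filtering.

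**The crossover supplies its own control.** Each participant uses the same checklist on placebo, so the placebo column shows background reporting within the same person. This largely stands. What remains is inflated absolute frequencies and possible dilution at participant level, with no built-in bias towards either treatment. Worsening of an existing item is also still visible in its burden rating.

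**Three stronger inferences are not supported.**

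- Section 6.6 says "The titration will be stopped at the onset of side-effects (as reported by the participant", and a reader might conclude that background symptoms lower the recorded maintenance dose. The wording refers to onset and does not tie the rule to logbook ticks, so that is conjecture.
- Section 1.3 mentions "the side-effect burden of poly-analgesic-pharmacy", but as an argument against prescribing several analgesics. It does not say that these participants carry that burden.
- The absence of a baseline concerns adverse events only. The primary outcome and the other participant-reported outcomes do use one.

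**Table layout and treatment-emergent rules often belong in an analysis plan.** That is true of such rules in general. Here the protocol itself fixes the collection schedule and the two-group presentation.

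**Conclusion.** The point holds in a limited form. Section 8.3.1 and Table 1 disagree on whether side effects are logged before treatment and on whether the baseline starts on day -8 or day -7. Under either reading, the adverse-event summary has no baseline, so symptoms present before dosing can be counted in both periods.

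The consequence is inflated absolute frequencies and, for participant-level proportions, a difference reduced by the factor 1 - b. That is a loss of 10% to 50% across the assumed backgrounds of 10% to 50%. These rates are assumptions, as is independence of background and new symptoms; the protocol gives no rate, so the true size is unknown. The outcome affected is secondary and descriptive, in a study that calls itself explorative, and the placebo period partly controls for background. The change is still worth making because it is cheap, and because baseline symptoms cannot be collected afterwards.

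**What to change.** 1. In section 8.3.1, state that the same symptom checklist and burden rating are completed daily in the baseline week, as Table 1 shows. Use one start day in both places, and make clear that the dose entry does not apply before treatment.
2. In section 10.2.1, add a baseline column for symptoms and burden. Add a supplementary descriptive summary of items that are new or worse than baseline, alongside the all-event counts and not in place of them.
3. Leave the wording of the on-treatment form, the adverse-event recording in section 9.2.1 and the titration rule as they are. The checklist stays comparable across periods only if its wording is the same throughout.

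The cost is about a minute of extra survey time a day in a week when the online logbook is already open, plus one table column and one summary. One limit remains: a baseline taken before day 1 is less close to the second period, which starts on day 29, and Table 1 shows no logging in washout. The new-or-worse summary is therefore less secure for that period, which is a further reason to keep it supplementary.
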